### Randomization

The randomization approach, followed by the COBIN first trial on hypertension in Lekhnath Municipality, will be repeated in this study [30]. Out of 15 wards (clusters) in the municipality, one will be randomly excluded before randomization by lottery method. The remaining 14 clusters will be randomly assigned to the intervention and control group in 1:1 allocation ratio. The estimated sample size for the intervention study will be 1143. To include the study participants from every different sized clusters (wards), the required sample size of 1143 will be multiplied by the proportion of eligible participants in the ward. Then the intervention participants from each ward will be randomly selected. Research assistants will be blinded to the participants’ allocation status. To avoid selection bias following measures will be taken: (a) the randomization of the clusters will be done after the baseline survey, (b) clusters will not be withdrawn or added to the study, and (c) an independent epidemiologist will randomize the clusters.

### Recruitment procedures

The sampling frame of the COBIN study [30], including a population framework of all eligible participants using the election voter’s list for 2007, will be adapted. The COBIN study baseline survey used this voter list and prepared a list of eligible respondents to participate in the trial. From the framework, we will list all individuals aged 40 years and above. The voter list provides information on name, age, household number, and address. Simple random sampling will be applied to select households. Kish method will be applied if more than one eligible participant from the same household exists during data collection [45]. During the baseline survey, participants will be identified and requested to participate in the study by the data enumerators at the participant’s household. After completing the survey, eligible participants will be randomly selected proportionately, with cluster size meeting the required sample size of 1143. On the final day of the training, FCHVs from each cluster will sit together and allocate the number of households to be visited during the intervention.

### Study intervention

Following randomization of the clusters, FCHVs falling in the intervention arm will receive six days of training on COPD, prevention, and management. Based on information from the baseline survey FEV_1_ and FEV_1_/FVC measures, participants will be categorized into two categories: healthy individuals, those at risk of COPD, and COPD patients. The interventions will then be designed accordingly, targeting each of these three groups. It includes home-based health education, tailored intervention, and referral for treatment, respectively, which FCHVs will deliver in three routine visits throughout the intervention period of 12 months. All three groups in the intervention arm will be exposed to home-based health education. Those at risk and those identified with COPD will additionally also be exposed to the tailored intervention, and those with COPD will also be actively motivated for treatment.

The home-based health education will include efforts from FCHVs: (1) to improve knowledge on COPD by providing basic information on COPD, its risk factors, symptoms, and its progression; (2) counseling the households on reducing and avoiding exposure to the risk factors (e.g., household air pollution and tobacco) of COPD; (3) ways of improving indoor air quality. Educational materials will be developed for their guidance with a focus on pictorial information. These materials will be developed in consultation with a pulmonologist, health education experts in the National Health Education and Information Centre of Government of Nepal, nurses, FCHVs, local health workers, patients living with COPD, and other stakeholders. The educational materials will be pretested among the FCHVs of Pokhara , a comparable area nearby not included in the study area.

The tailored intervention, which will target those at risk and those with COPD, will include the following: (1) information to avoid exacerbations and maintain general lung health (exposure reduction, exercise, sleep, and nutrition), (2) information on the hazards of cigarette smoking, (3) advice on smoking cessation, (4) suggestions for maintaining improved cooking stoves, and (5) better indoor cooking environment with adequate ventilation. Those who show willingness towards quitting smoking will be continually motivated by the FCHVs and followed up during their routine visits. For those with COPD, FCHVs will assess the COPD status using COPD status assessment guides for FCHVs (CAF guide) designed with basic questions on cough, breathing problems, and daily functioning activities. Thus, they recommend referring to hospitals, suggesting being physically active, and counseling on proper nutrition. In addition, FCHVs will also teach persons with COPD about the basic breathing techniques (purse lip breathing, deep breathing, and diaphragmatic breathing) added with stamina and endurance-building exercises.

### Usual care in control clusters

The usual care will include whatever prevention or treatment services are available at present. After 12 months of intervention, a follow-up survey will be conducted by trained data enumerators.

### Analysis

The primary and secondary aims of this study will be assessed using an intent-to-treat analysis. The primary outcome of the study will be the average difference in the rate of decline of FEV_1_ and FEV_1_/FVC between the intervention and control arms. We will use a mixed model ANOVA to test the statistical significance of the difference in the rate of change of primary outcomes between the intervention and control arms. Potential confounder variables statistically significantly associated with treatment assignment will be included in the multivariable analysis.

Our secondary outcomes include the change in the quality of life among people living with COPD, awareness, and knowledge on COPD, and change in magnitude of risk factors of COPD. The quality of life will be measured using the validated Nepali version of the St. George Respiratory Questionnaire [43]. The change in the quality of life will be assessed using the difference in the mean or median score at the beginning and end of the intervention accompanied by the standard deviation or interquartile range of the difference. The change in awareness and knowledge related to COPD will be assessed using the change in the proportion of people aware and knowledgeable regarding COPD. Similarly, the change in risk behaviors, including smoking and indoor cooking, will be assessed by measuring the proportion of individuals who changed those behaviors in the intervention and control clusters. The subgroup analysis will be performed based on COPD status, grade, and smoking status. Complete case analysis will be done for missing data less than 10%. In case of missing data for more than 10%, it will be addressed by the multiple imputation method. We will explain the effect of non-adherence and missing data on our results. Participants receiving three routine home visits by FCHVs during the intervention period will be considered complete adherence. We will assess two-way interaction among sex and treatment allocation, and also among smoking status and treatment allocation. STATA software (StataCorp, College Station, TX, USA) will be used for the data analysis of the study.

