**Method:**

This study aims to evaluate the effect of a community-based health educational intervention administered by Female Community Health Volunteers (FCHVs) on the prevention and management of COPD. An open-label, two-group, community-based, cluster-randomized controlled trial will be implemented in the semi-urban area of Pokhara Metropolitan city (former Lekhnath Municipality) located in the Kaski district of Nepal. The estimated sample size of the intervention will be 1143. The unit of randomization is the ward (administrative unit) of the study area. The follow-up survey will be conducted immediately after 12 months of FCHVs-led interventions. The difference in the rate of decline of forced expiratory volume in 1 s (FEV_1_) and FEV_1_/FVC (forced vital capacity) ratio are the primary outcomes and the change in the proportion of modifiable risk factors of COPD, health-related quality of life scores, and change in knowledge of COPD will be secondary outcomes.

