### Sample size calculation

In the absence of a relevant Nepali study to take reference from for prevalence study, the sample size for this study is estimated according to the method suggested in the WHO STEPwise approach assuming the prevalence of COPD in Nepal to be 8% (a figure obtained from a Chinese study [34] and global burden of disease study based projection for Nepal [35]). When stratified by age group and sex (altogether eight groups in both sexes: 40–49, 50–59, 60–69, and ≥ 70), the sample size is 1508, when considering a 5% margin of error and expected response rate of 90%. Likewise, taking reference from a Chinese trial on community-based management of COPD for the expected mean difference between intervention and control arm as 19 ml FEV_1_ with a design effect of 1.83, considering an intracluster correlation of 0.01, the number of clusters per arm being 7, total sample size per arm will be 476 [36]. The coefficient of variation 0.45 was taken based on a previous study conducted in the same population [37]. Thus, the sample size required in the intervention for 80% of power and allowing 20% loss to follow-up will be 1143.

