### Study outcomes

The primary outcome will be the rate of decline in FEV_1_ and FEV_1_/FVC ratio in the intervention and control groups from baseline and follow-up. The secondary outcomes will include the change in awareness and knowledge related to COPD, quality of life of COPD patients, modification of risk factors of COPD such as active and passive smoking and change in indoor cooking behavior from baseline between the intervention and control clusters. The questionnaire-based interview and spirometry during the baseline and follow-up survey will be conducted in participants’ households using a portable diagnostic spirometer by data enumerators trained for 3 weeks.

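### Two primary outcomes are declared and tested, but the sample size and 80% power rest on FEV1 alone, so what counts as a positive trial, and with what error and power, is not fixed

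*Protocol article*

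**What the plan says.** Three places in the protocol article define the primary endpoint, and each names the same two quantities.

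- Abstract, Method: the differences in decline of FEV1 and of the FEV1/FVC "ratio are the primary outcomes".
- Analysis: "The primary outcome of the study will be the average difference in the rate of decline of FEV_1_ and FEV_1_/FVC".
- Study outcomes: "The primary outcome will be the rate of decline in FEV_1_ and FEV_1_/FVC ratio in the intervention and control groups".

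The Analysis section then commits to testing them: "We will use a mixed model ANOVA to test the statistical significance of the difference in the rate of change of primary outcomes". It does not order the two, divide the significance level between them, or say whether one or both must be significant.

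The sample size section uses only one of them. It takes the "expected mean difference between intervention and control arm as 19 ml FEV_1_ with a design effect of 1.83", with an intracluster correlation of 0.01, 7 clusters per arm and a coefficient of variation of 0.45. It arrives at 476 per arm and, for 80% power with 20% loss, 1143 in total. No effect size, standard deviation or power is given for FEV1/FVC. The only 5% in that section belongs to the prevalence survey: "the sample size is 1508, when considering a 5% margin of error".

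**The concern.** A volume and a ratio cannot be combined into one estimate without a defined composite, and none is defined, so the trial will produce two primary tests. With equal standing and no order, there are two natural ways to read a result, and each upsets one of the design's operating characteristics:

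- If one significant result is enough, two chances of a false positive are taken and the overall error exceeds the level of each test.
- If both must be significant, the stated 80% no longer describes the chance of a positive trial, because it covers FEV1 only.

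The two outcomes can also disagree. If FEV1 and FVC fall together, the ratio need not move. The protocol article would then give no verdict, and the choice of which result to headline could be made after the results are known.

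**Working it through.** **Inputs from the protocol article (Sample size calculation, Trial Design):** 476 per arm; 1:1 allocation; 20% loss; 80% power; 19 ml difference in FEV1; design effect 1.83.

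**Assumptions (not in the document):** two-sided 5% for each test; jointly normal test statistics; correlation r between the two test statistics varied from 0 to 0.9; where joint power is computed, 80% power for FEV1/FVC.

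**1. The plan's own figure.** 2 × 476 = 952, and 952 × 1.2 = 1142.4, rounded up to 1143. The total is reproduced, and nothing in it comes from FEV1/FVC. The 476 itself cannot be derived independently, because no standard deviation is stated.

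**2. Success on either outcome.** Risk = 1 − P(|Z1| ≤ 1.96 and |Z2| ≤ 1.96) when neither outcome is affected.

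| r | False-positive risk |
|---|---|
| 0 | 1 − 0.95² = 9.75% |
| 0.5 | 9.1% |
| 0.7 | 8.3% |
| 0.9 | 7.0% |

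Independence gives the maximum for jointly normal statistics. The figures depend on the assumed level: at r = 0 the risk would be 1 − 0.99² = 1.99% with 1% per test and 1 − 0.90² = 19% with 10% per test.

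**3. Success only if both are significant.** There is no inflation above the level of each test. Joint power cannot exceed the power for FEV1, so it is at most 80%. If FEV1/FVC also had 80% power, joint power = P(Z1 ≤ 0.842 and Z2 ≤ 0.842):

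| r | Joint power |
|---|---|
| 0 | 0.8 × 0.8 = 64% |
| 0.5 | 69% |
| 0.9 | 75% |

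If power for FEV1/FVC is lower than 80%, these figures fall further.

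**4. Splitting the level, 2.5% each.** This controls the error (1 − 0.975² = 4.94% if independent) but costs power for FEV1. The planned size gives a standardised effect of 1.960 + 0.842 = 2.802. Against a critical value of 2.241, power is Φ(2.802 − 2.241) = Φ(0.56), about 71%. Restoring 80% multiplies the size by ((2.241 + 0.842)/2.802)² = 1.21, and 476 × 1.21 is about 577 per arm. With the plan's own factor, 2 × 577 × 1.2 = 1384.8, or 1385 in total.

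**5. Fixed sequence, FEV1 first.** FEV1 is tested at the full 5%, so its planned power is untouched. FEV1/FVC is tested at 5% only after FEV1 is significant, so the overall error stays at 5% whatever the correlation. The sample size is unchanged.

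**The case against.** The strongest reply is that a multiplicity rule is routinely left to the statistical analysis plan, which is not shown, and that a journal article condenses its source. That stands as far as it goes: the absence of a rule is not in itself an error here, and an analysis plan that puts FEV1 first would be compatible with the printed sample size. What remains is visible in the article: two outcomes are given equal primary standing while one sample size and one power figure cover only the first. The success rule determines whether that power figure is true.

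A reader might infer that the trial runs a 9.8% false-positive risk. The document does not support that. It states no significance level for the trial tests and does not adopt an either-outcome rule; joining the two outcomes with a simple conjunction can equally mean that both are required. Independence, which the top figure needs, is also implausible because FEV1 is the numerator of the ratio. Nor can a reader conclude that the trial is underpowered: that holds only under a both-required or split-level rule, and power for FEV1/FVC is unknown.

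The shift between singular and plural for the primary outcome is not a point of substance. All three places clearly intend the same two measures.

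Finally, making one declared primary depend on the other after recruitment has closed is more than an edit of wording. That objection is right and is reflected in the cost below.

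**Conclusion.** The point holds in this form: two equal primary outcomes are fixed and tested, against a sample size and 80% power computed for FEV1 only. At an assumed two-sided 5% per test, an either-outcome claim carries about 7.0% to 9.75% false-positive risk, with the lower part of the range more plausible. A both-required claim is not inflated, but its power is at most 80%, and 64% to 75% for correlations from 0 to 0.9 if FEV1/FVC were also powered at 80%. The facts about the document are certain. The sizes depend on the assumed level, the unknown correlation and the unstated power for FEV1/FVC. The matter affects how the main result may be interpreted and should be settled before analysis.

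**What to change.** Before the outcome data are analysed, set a fixed testing sequence: the between-arm difference in FEV1 decline first, at two-sided 5%, then FEV1/FVC at two-sided 5% only if FEV1 is significant. State that the 80% power refers to FEV1. FEV1 goes first because it is the outcome on which the trial was sized. FEV1/FVC may keep the label of primary outcome, second in order. Use the same wording in the abstract, Analysis and Study outcomes.

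The cost is a protocol amendment, reported as the Trial management section requires to the ethics board, the DSMB, the FCHVs, the trial registries and the journals. FEV1/FVC can then no longer support a positive claim by itself. The sample size does not change. That matters because the Trial status section says recruitment ended in September 2019, so options that need more participants, such as the split level in step 4, could not be restored to 80% power.

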### Trial Design

A community-based, two-armed, open-label cluster-randomized controlled trial will be conducted in the semi-urban area of the Kaski district of western Nepal. It will be a parallel-group superiority trial with an allocation ratio of 1:1. The intervention time will be 12 months with assessments of outcomes at baseline and follow-up of the study.

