### Survey tools

The survey tool includes information on socio-demographic information, behavioral information, and relevant questions on respiratory conditions. Spirometry will accompany the questionnaire survey. Data enumerators with minimum qualification of a bachelor’s degree in health sciences will be trained to measure lung function using diagnostic portable spirometers and conducting an interview using the survey questionnaire.

The questionnaire to be used in the baseline and follow-up will be adapted from the WHO STEPwise Surveillance tool and similar past studies that measured the burden of lung disease and its risk factors [34, 36, 38–42]. St. George’s respiratory questionnaire, which has been adapted and validated for use in Nepal, will also be used for COPD patients [43]. The socio-demographic information includes age, sex, education, occupation, and income. Lifestyle variables comprise detailed smoking history (current/former, type of tobacco use, intensity, and duration), environmental exposure to tobacco smoke at home or workplace, household fuel type use, and exposure to biomass fuel. Participants’ blood pressure, weight, and height will be measured, and body mass index calculated.

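### Covariates for the multivariable analysis are chosen by a significance test against arm, so chance imbalance sets the model and prognostic baseline variables are usually left out

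*Protocol article*

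**What the plan says.** Two adjacent sentences in the Analysis section matter. The first gives the primary test: "We will use a mixed model ANOVA to test the statistical significance of the difference in the rate of change of primary outcomes". It names no covariates. The second gives the adjustment rule: "Potential confounder variables statistically significantly associated with treatment assignment will be included in the multivariable analysis". No other criterion for entering the multivariable analysis is stated, no covariate is listed, and the article does not say whether that analysis is primary or supportive.

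Under Randomization, "the randomization of the clusters will be done after the baseline survey", and "The remaining 14 clusters will be randomly assigned to the intervention and control group in 1:1 allocation ratio". No stratification or matching is described.

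Under Survey tools, "The socio-demographic information includes age, sex, education, occupation, and income"; "Lifestyle variables comprise detailed smoking history"; and "blood pressure, weight, and height will be measured, and body mass index calculated". Spirometry is done at baseline as well. In the Analysis section, sex and smoking status appear only as interaction or subgroup terms. Trial Design fixes two outcome times: "The intervention time will be 12 months with assessments of outcomes at baseline and follow-up of the study".

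**The concern.** A test of association between a baseline variable and arm asks whether the allocation was random. Here it was, by design. A small p-value therefore marks a chance imbalance and says nothing about whether the variable predicts decline in lung function. The rule can admit an imbalanced variable of little prognostic value, and it drops a prognostic one whenever its imbalance falls short of significance.

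Two things are at stake. The adjusted model cannot be known until the data have been examined, so it is not prespecified. And the precision that the baseline survey could supply is mostly given up, in a trial with only seven wards per arm and a target difference of 19 ml in FEV1.

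This is more than a detail left to an analysis plan: the article itself fixes the selection criterion.

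**Working it through.** **Inputs.** From Sample size calculation: 476 per arm, 7 wards per arm, intracluster correlation 0.01, coefficient of variation 0.45, design effect 1.83, difference 19 ml, power 80%, 20% loss to follow-up. A two-sided 5% level is assumed, because none is stated.

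**The plan's own figures.** 2 × 476 × 1.20 = 1142.4, which rounds up to the stated 1143. With 476/7 = 68 per ward, 1 + ((1 + 0.45²) × 68 − 1) × 0.01 = 1.81, close to the stated 1.83 (70 per ward gives 1.83). The concern does not change these figures.

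**How often the rule omits a prognostic variable.**
- Valid test at 5%: selected in 5% of randomisations, omitted in 95%.
- Test that ignores wards, giving the covariate the plan's design effect: 2 × (1 − Φ(1.96/√1.83)) = 0.147, so omitted in about 85%.

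Neither figure depends on how strongly the variable predicts outcome.

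**Power if covariates are fixed in advance.** The unadjusted noncentrality at 80% power is 1.96 + 0.84 = 2.80. Suppose the covariates explain a share R² of the outcome variance (5–20%, assumed).
- If they explain variance within and between wards alike, power = Φ(2.80/√(1 − R²) − 1.96).
- If they act only within wards, about 1/1.83 = 55% of the variance of the estimate can be reduced, so 1 − R² becomes 1 − R²/1.83.

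| R² | Within wards only | Within and between wards |
|---|---|---|
| 0.05 | 81% | 82% |
| 0.10 | 82% | 84% |
| 0.20 | 84% | 88% |

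**Behaviour of the rule itself.** A simulation of 10,000 trials per setting used 14 wards of 68, intracluster correlation 0.01, one covariate, ward-level analysis on 12 degrees of freedom, and selection by a participant-level test. The covariate acted at both levels and its true coefficient was used. The covariate–outcome correlations are assumed.

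| Correlation (R²) | Variance vs unadjusted: always adjust | Variance vs unadjusted: plan's rule | Type I error: plan's rule |
|---|---|---|---|
| 0.3 (0.09) | 0.91 | 0.96 | 5.0% |
| 0.5 (0.25) | 0.74 | 0.86 | 4.0% |
| 0.7 (0.49) | 0.51 | 0.75 | 3.1% |

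The rule captures roughly half of the available variance reduction. Its error rate falls below 5% because large imbalances are corrected, while in the remaining trials the standard error is still the unadjusted one. At R² = 0.09, within the assumed range, the error rate stays nominal. The drift appears only with stronger covariates.

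**Baseline FEV1 as a covariate.** Against a raw change score, modelling follow-up on baseline multiplies the variance by (1 + ρ)/2. That is 0.975 to 0.90 for baseline-to-follow-up correlations of 0.95 to 0.80 (assumed), a cut of 2.5–10%.

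**The case against.** **The primary test may not depend on the rule.** The mixed-model sentence comes first and carries no covariates. If the multivariable analysis is supportive, the headline p-value is untouched. This stands: the text does not settle it, and the omission is itself something to correct.

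**Baseline FEV1 is not simply left out.** A reader might infer that an imbalance in baseline FEV1 goes uncorrected against a 19 ml target. The outcome is a change between two times, so most of that imbalance is differenced out. Only (1 − ρ) of it remains, 5–20% at the correlations above. The objection stands, so the loss concerns mainly the other baseline variables.

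**No inflation of false positives is shown.** A reader might infer that data-driven selection makes the test anti-conservative. The simulated error rates are nominal or below, so that reading fails.

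**Spurious selection is easily overstated.** With ten candidates (assumed), at least one is flagged with probability 1 − 0.95¹⁰ = 40% under valid tests, or 1 − (1 − 0.147)¹⁰ = 80% if wards are ignored. Both figures need ten independent tests, which is implausible for sex, height, smoking and body mass index. The second also needs tests that ignore wards, which the article does not say, and gives the covariates the outcome's design effect. Neither figure supports the conclusion here.

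**Limiting the rule to potential confounders may imply a prior screen for relevance.** Possibly, but no list or criterion is given. A screen would not cure the omission of prognostic variables that happen to be balanced.

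**Conclusion.** The concern holds in a limited form. The article makes a significant association with arm the only stated route into the multivariable analysis, and in a trial randomised after the baseline survey that association is chance. The covariate set becomes data-driven, and a prognostic variable is omitted in about 85–95% of randomisations.

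The harm is to precision and prespecification. Relative to an unadjusted analysis, the power forgone is about 1–4 percentage points if covariates act only within wards, and at most 2–8 if they also explain between-ward variance. This rests on an assumed R² of 5–20%; nothing in the article shows how well age, sex, height or smoking predict 12-month change. The figures refer to FEV1, the only outcome in the power calculation.

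The documents do not support saying that the primary test is compromised, that type I error is inflated, or that baseline FEV1 is ignored.

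**What to change.** Delete the significance-test rule and amend the Analysis section as follows.

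- Name a short prognostic set in advance, for example age, sex, height and baseline smoking status, kept small because there are 14 wards. State that no covariate is chosen by a test of baseline balance.
- State whether this adjusted analysis is primary or supportive.
- Choose one use of the baseline outcome. Either model follow-up FEV1 and FEV1/FVC with the baseline value as a covariate and a ward random effect, rewording the mixed model ANOVA sentence to match, or keep baseline as a repeated measure. Doing both would use the same measurement twice.
- Report the analysis adjusted only for the baseline outcome as a sensitivity analysis.
- Date the change and state whether outcome data by arm had been seen. Trial status places the endpoint assessment at the end of March 2021, so the timing matters to a reader.

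The cost is small: the list must be fixed in advance and the model sentence reworded. No new data are needed and the sample size is unaffected.
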